## Abstract

**Background:**

In 2003, the governments of Belgium, France, Germany, the Netherlands and Switzerland agreed that there was a need in Europe for a treatment programme for adolescents with cannabis use disorders and other behavioural problems. Based on an exhaustive literature review of evidence-based treatments and an international experts meeting, Multidimensional Family Therapy (MDFT) was selected for a pilot study first, which was successful, and then for a joint, transnational randomized controlled trial named INCANT (INternational CAnnabis Need for Treatment).

**Methods/design:**

INCANT is a randomized controlled trial (RCT) with an open-label, parallel group design. This study compares MDFT with treatment as usual (TAU) at and across sites in Brussels, Berlin, Paris, The Hague and Geneva. Assessments are at baseline and at 3, 6, 9 and 12 months after randomization. A minimum of 450 cases in total is required; sites will recruit 60 cases each in Belgium and Switzerland, and a maximum of 120 each in France, Germany and the Netherlands.

Eligible for INCANT are adolescents from 13 through 18 years of age with a cannabis use disorder (dependence or abuse), with at least one parent willing to take part in the treatment. Randomization is concealed to, and therefore beyond control by, the researcher/site requesting it. Randomization is stratified as to gender, age and level of cannabis consumption.

Assessments focus on substance use; mental function; behavioural problems; and functioning regarding family, school, peers and leisure time.

For outcome analyses, the study will use state of the art latent growth curve modelling techniques, including all randomized participants according to the intention-to-treat principle.

INCANT has been approved by the appropriate ethical boards in Belgium, France, Germany, the Netherlands, Switzerland, and the University of Miami Miller School of Medicine. INCANT is funded by the (federal) Ministries of Health of Belgium, Germany, the Netherlands, Switzerland, and by MILDT: the Mission Interministerielle de Lutte Contra la Drogue et de Toximanie, France.

**Discussion:**

Until recently, cannabis use disorders in adolescents were not viewed in Europe as requiring treatment, and the co-occurrence of such disorders with other mental and behavioural problems was underestimated. This has changed now.

Initially, there was doubt that a RCT would be feasible in treatment sectors and countries with no experience in this type of study. INCANT has proven that such doubts are unjustified. Governments and treatment sites from the five participating countries agreed on a sound study protocol, and the INCANT trial is now underway as planned.

**Trial registration:**

ISRCTN51014277

## Background

In 1999, the (junior) Ministers of Health of five Western European countries - Belgium, France, Germany, the Netherlands, and Switzerland - concluded that their countries were fighting each other over cannabis policies without sufficient scientific evidence to support any view. They agreed to combine scientific efforts. Based on a systematic literature review and the recommendations of an international group of experts [1], the Five-Countries Action Plan for Cannabis Research was adopted in April 2003. It stressed the need of a transnational trial to test an outpatient treatment of cannabis use disorder in youth who may have other problems as well. The Plan acknowledged that adolescents are sensitive to developing cannabis use disorder, which is not easily overcome without treatment [2].

The treatment selected in the Action Plan was Multidimensional Family Therapy (MDFT), developed since 1985 by [name] and co-workers at the Center for Treatment Research on Adolescent Drug Abuse (CTRADA), University of Miami Miller School of Medicine [2]. MDFT is a family based outpatient treatment programme for adolescent problem behaviour. The term 'multidimensional' reflects the assumption that each major domain in the life of an adolescent may contribute to the incidence and persistence of behavioural problems (through risk factors) and may help in resolving such problems (through protective factors). The life domains include the youth itself, parent, family, friends and peers, school and work, and leisure time. The therapist conducts therapy sessions - with multiple therapeutic alliances: with both the adolescent and the parents -, but also sets out to improve life domain conditions for the adolescent and the family in an outreaching and pragmatic fashion. MDFT views family functioning as instrumental in creating new, developmentally adaptive lifestyle alternatives for the adolescent. Skills training includes substance use relapse prevention, family communication, and parenting. MDFT has been tested with success in different adolescent populations, doses and treatment delivery settings [3,4].

Once it had been decided that a trial was called for, implementation hurdles had to be overcome and confidence in the feasibility of a trial had to be boosted. Although the existence of cannabis use disorder among adolescents had been accepted at the time INCANT was planned, there were quite a few policy makers and therapists who thought that youth with such a disorder, and their families, would not be interested in seeking help, let alone in joining a trial. It was feared that INCANT would fail in recruiting enough subjects, because a (real-world) RCT was still exotic and controversial in Western European youth care at the time. Also, there was concern that a treatment like MDFT, because it is manual-based and time-limited, would stand no chance in countries such as France with a dominant psycho-analytic treatment tradition. Similarly, MDFT was thought to meet opposition in Germany, where treatment of substance abusing adolescents often lasted for more than 1 year. Further, therapists from some of the participating countries - such as Switzerland - believed that mandatory urine tests of alcohol and drug use, which are common practice in American addiction care and a recommended part of MDFT, would not be acceptable to European adolescents.

In view of all this, the five countries carried out a pilot study first to examine the feasibility of a trial of MDFT in Western Europe. Therapists from all participating countries were successfully trained to adequate levels of MDFT adherence and competence as specified in the treatment manual [5]. The potential for recruiting cases for treatment and for study purposes appeared to be promising, and substance urine tests were accepted by virtually all families considered in the pilot study. MDFT could be properly applied, despite variation between the five European countries in mainstream theoretical treatment orientation, personnel requirements, and reimbursement policies.

Because of the generally positive results of this pilot [6], the countries had a protocol prepared for a main study, named INCANT (INternational CAnnabis Need of Treatment). INCANT was to be organized on a transnational basis, with input from all participating countries and with the prospect of helping to create a joint European treatment research infrastructure.

We here report on the design of INCANT.

## Methods/Design

### Design

INCANT is a multicentre phase III(b) randomized controlled trial with an open-label, parallel group design. This study compares MDFT with treatment as usual (TAU) at and across sites in Brussels, Berlin, Paris, The Hague and Geneva. Assessments are at baseline (immediately before randomization) and at 3, 6, 9 and 12 months after randomization.

### Approval

INCANT has been approved by the Ethical Board of Brugmann University Hospital (Belgium), the committee for public law issues of the Chamber of Psychological Psychotherapists and Child and Adolescent Therapists in the state of Berlin (Germany), the Hotel-Dieu Committee for the Protection of Human Subjects in Biomedical Research (CCPPRB; France), the medical-ethical committee for research in mental health care settings (METiGG kamer Noord; the Netherlands), the Ethical Board for Clinical and Outpatient Research (Medical Association of the Geneva Canton; Switzerland), and by the Institutional Review Board of the University of Miami Miller School of Medicine. These boards monitor the progress of the study in terms of recruitment, drop-out and the possible incidence of untoward events.

### Treatment centres

In 2003, government representatives from Belgium, France, Germany, the Netherlands and Switzerland nominated candidate youth outpatient treatment centres for taking part in the pilot study preceding INCANT. The project leader (HR) and CTRADA staff from Miami visited the nominated centres. They selected the department of psychiatry of Brugmann University Hospital in Brussels; Therapieladen in Berlin; Centre Emergence in Paris with suburban CEDAT (Conseils Aide et Action contre le Toximanie) sub-sites in Mantes la Jolie and St Germain en Laye; and the twinning sites of Parnassia Brijder (Mistral, youth addiction care) and De Jutters (Palmhuis, youth forensic care) in The Hague. All these sites did well in the pilot study [6] and have joined the INCANT trial. In Switzerland, the pilot study sites in Zurich, Basle and Bern were replaced by Phénix (Geneva) for the actual trial, as the potential for recruiting substance abusing adolescents was better there.

### Participants

Eligible for INCANT are adolescents of either sex, from 13 through 18 years of age, with a cannabis use disorder (dependence or abuse), with at least one parent willing to take part in the treatment. The word 'parent' denotes any legal representative of the adolescent (including step or foster parent, or guardian). We use the singular 'parent' here, also including the plural 'parents'. Adolescent and parent together are referred to as a 'case'.

Adolescents are ineligible if unable to understand - IQ lower than 70 - the local language, unable to attend outpatient sessions, or if suffering from a mental or behavioural disorder requiring inpatient treatment. Parents (and therefore cases) are ineligible if unable to understand the local language or attend sessions.

Informed consent for study participation is obtained from both adolescent and parent.

### Sample size

We carried out power calculations to determine the number of subjects needed to establish treatment effects on substance use measures within and across sites. To this end, we applied Monte Carlo simulation techniques with latent growth curve models [7]. A large number of samples were drawn, systematically varying effect size estimates, and a model was constructed for each sample. Each simulation tested a linear growth model for continuous outcomes with four time points (0, 6, 9 and 12 months), representing the four major INCANT assessment points. The result of interest was the regression coefficient between a dichotomous covariate representing treatment condition and the latent slope representing change in substance use over time.

In previous trials of MDFT [[4], for review] the size of the comparative treatment effect - the extent in which MDFT outperformed active control treatments - has generally been in the moderate to high range [8] of *d *= 0.6 or above. Conservatively assuming small effects, the models we generated predicted that power would be above 0.9 if the total cross-site sample consisted of 450 or more cases. For individual site analyses, assuming an effect size of 0.7, a sample of 100 per site would be needed to achieve power of 0.82.

We set the recruitment target at 480 cases. The sites in Germany, France and the Netherlands aim to recruit a maximum of 120 cases each. Because of budget limitations, Belgium and Switzerland settle for 60 cases each, with the intention to contribute to the cross-site statistical analyses.

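### The claim of power above 0.9 at 450 cases for small effects gives no effect size, and the protocol's own site figure supports it only for d of about 0.37 or more

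*Protocol article*

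**What the plan says.** The Sample size section of the protocol article describes one method: Monte Carlo simulation of a linear latent growth model at 0, 6, 9 and 12 months. The parameter of interest is the effect of treatment on the latent slope, and the effect size was varied across simulations. Two results follow.

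- Pooled analysis: "Conservatively assuming small effects, the models we generated predicted that power would be above 0.9 if the total cross-site sample consisted of 450", as a minimum. No numeric effect size is attached.
- Single site: "assuming an effect size of 0.7, a sample of 100 per site would be needed to achieve power of 0.82".

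The only size label tied to a number concerns earlier trials of the experimental treatment. Their advantage over active controls "has generally been in the moderate to high range", with d of 0.6 or above. The article gives no alpha, sidedness, attrition rate or growth-model variance for either result.

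The pooled result supports the sample size. The Abstract says "A minimum of 450 cases in total is required", and the Sample size section sets the target at 480 (three countries at up to 120 and two at 60).

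**The concern.** Both results are reported from the same model and the same tested coefficient. What visibly differs is the effect size and the number of cases. In that setting one result largely determines the other, so the site figure can be used to ask which effect the pooled figure must have assumed. The answer is larger than most readers would take from a conservative assumption of small effects.

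What is at stake is the justification of the 450-case minimum. The Analyses section makes the pooled analysis the main one. The Sample size section accepts 60 cases each in Belgium and Switzerland because of budget limits, on the ground that they contribute to it. A reader should be able to tell which effect that analysis can detect with power 0.9.

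**Working it through.** **Inputs from the Sample size section.** Site: effect size 0.7, N = 100, power 0.82. Pooled: N = 450, power above 0.9, effect size unnumbered. Target N = 480.

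**Assumptions of this review.** Alpha 0.05 two-sided unless noted; 1:1 allocation; d = 0.2 as the conventional small effect, with a range shown.

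**1. Can the stated figures be reproduced?** The pooled figure cannot, because it has no numeric d. The site figure can be set against a plain two-group comparison, with non-centrality d × √N / 2:

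- 0.7 × 10 / 2 = 3.5, so power = Φ(3.5 − 1.960) = 0.938 (t-test 0.934), against 0.82 stated.
- A loss of 30% to 35% gives 0.834 to 0.806, and alpha 0.01 two-sided gives 0.822. The article states neither.

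The growth-model variances are not printed, so the simulation cannot be rerun. The stated site figure lies below the plain comparison.

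**2. Scale the site figure to the pooled sample.** Within one model the non-centrality is k × d × √N.

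- Site: z(0.975) + z(0.82) = 1.960 + 0.915 = 2.875, so k = 2.875 / (0.7 × 10) = 0.4108.
- N = 450, d = 0.2: 0.4108 × 0.2 × 21.21 = 1.743; power = Φ(1.743 − 1.960) = 0.414. Rounding of 0.82 allows 0.410 to 0.419. One-sided testing gives 0.463.
- d for power 0.90, which needs 1.960 + 1.2815 = 3.2415: 3.2415 / (0.4108 × 21.21) = 0.372 at N = 450, and 0.360 at N = 480. One-sided at N = 450 it is 0.377.

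A random-slope model at 0, 6, 9 and 12 months, with residual variance tuned to give 0.82 at the site values, returned 0.414 at d = 0.2 and 0.897 at d = 0.37 for each of four slope variances.

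**3. Power over a range of d (two-sided 0.05).**

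| d | Scaled, N = 450 | Scaled, N = 480 | Plain t-test, N = 450 |
|---|---|---|---|
| 0.20 | 0.41 | 0.44 | 0.56 |
| 0.25 | 0.59 | 0.61 | 0.75 |
| 0.30 | 0.74 | 0.77 | 0.89 |
| 0.35 | 0.86 | 0.88 | 0.96 |
| 0.40 | 0.94 | 0.95 | 0.99 |
| 0.50 | 0.99 | 0.99 | above 0.99 |

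The plain comparison at d = 0.2 gives 0.68 one-sided and 0.32 at alpha 0.01 two-sided. No variant tried at d = 0.2 left the range 0.32 to 0.68.

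**4. Reverse check.** If 450 cases did give 0.90 at d = 0.2, then k = 3.2415 / (0.2 × 21.21) = 0.764. A site would then need (2.875 / (0.7 × 0.764))² ≈ 29 cases for power 0.82 at effect size 0.7, not 100. Put differently, the pooled simulation would need (3.2415 / 1.743)² ≈ 3.5 times the information per case of the site simulation.

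**The case against.** A reader might infer that the two printed figures contradict each other and that the true pooled power is 0.41. The document does not support that. It never sets small at 0.2, and the two figures agree if the assumed effect was about 0.37 or more. That lies below the 0.6 labelled moderate to high, the only numeric anchor in the text.

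The scaling also rests on a common alpha, variances, attrition and effect metric. Since the site figure falls short of the plain comparison, some unreported ingredient is present and might not be common to both. If, say, alpha 0.01 had been used at site level only, a plain comparison at N = 450 and alpha 0.05 would reach 0.90 at d of about 0.31. So 0.41 is one point in a range. Both objections stand.

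A further objection is that a journal article may leave the d, alpha and growth parameters to the full protocol. As a complaint about missing detail, the point would fail. It survives because a printed label, a printed power and a printed companion result do not fit together at d = 0.2 under any variant tried. Even the 0.31 above exceeds the conventional small value, and 0.37 is nearer the conventional medium value of 0.5 than 0.2.

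A reader might also infer that the trial is too small, or that a null pooled result will be read as excluding a small effect. Neither follows. At d = 0.6 the scaled power at 450 cases is 0.999, and nothing in the document proposes that reading of a null result. Low power within a 60-case site is no defect either, since those sites are there for the pooled analysis.

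**Conclusion.** The point holds in conditional form. If the pooled and site results share their model, alpha, variances, attrition and effect metric, 450 cases give 0.90 power only for d of about 0.37 or more, and 480 cases for about 0.36. At d = 0.2, power is about 0.41 by scaling and at most 0.56 two-sided (0.68 one-sided) in a plain two-group comparison.

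The plain comparison is not a strict ceiling for every growth model, since d might be expressed in another metric. However, the protocol's own model falls below it at site level, and nothing in the text suggests that it would do better when pooled.

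On these assumptions one of two things needs correcting. Either the pooled power is too high for a small effect, or the assumed effect was about 0.37 or more and calling it conservatively small misdescribes it. The document does not show which.

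**What to change.** Check the sponsor's simulation output and state the d and alpha behind the pooled figure. Then reword the sentence so that label and power agree. A possible form, with every number to be confirmed from that output: with 450 to 480 cases the pooled analysis has power 0.90 for d of about 0.36 to 0.37, and power well below 0.9 (about 0.4 to 0.6) for d = 0.2. If small was meant as about 0.37 or more, one sentence saying so settles the point. If the two results used different alpha, attrition or variance settings, say so, because the scaling above would then not apply.

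The cost is a text change and one check of existing output. No added recruitment or change of design is needed. The stated figure becomes less favourable.

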### Recruitment

There are two recruitment annex baseline measurement meetings. The first session, generally with the adolescent and parent together, is carried out by the clinical supervisor of the treatment centre, except in Brussels where the (clinically trained) INCANT researcher serves as the 'front office'. In this session, all eligibility criteria are checked, including the adolescent's cannabis use, but as yet no diagnosis of cannabis use disorder is set. INCANT is explained, and youth and parent are given study information materials and informed consent forms to read before coming back for the second recruitment session generally held a few days later.

In this second meeting, all (remaining) baseline measurements are conducted, separately for youth and parent. If eligible - diagnosis of cannabis use disorder confirmed -, youth and parent are both invited to sign the respective informed consent form.

### Central database

Each site has one or two researchers authorized to access their own site's internet based location - part of the Erasmus MC managed INCANT central database (open source MySCL) -, but not the locations of the other sites. Only the Erasmus MC database manager has full access to all locations and is mandated to change inputted data if so instructed by the project leader (HR) on behalf of the international committee overseeing the design and execution of the trial, viz., the INCANT Study Team (IST).

When inputting data into the database, each case is identified by a code assigned by the database at the time randomization was requested. The INCANT privacy policy ensures that each researcher locally stores person identifying data in such a way that they are blocked from access by others and not become part of the database.

Each questionnaire or interview, per assessment point, has its own file in the database, formatted using PHP Surveyor version 1.0.

### Randomization

Randomization takes place right after having obtained informed consent.

In Belgium, France, Germany and Switzerland, we stratified the study sample using three dichotomous variables (gender; age [13-14 years vs. 15-18 years]; and level of cannabis use in the past 90 days [74 or fewer days of cannabis consumption vs. 75 or more]). In the Netherlands, we added the stratification variable 'ethnicity' (adolescents classified according to national census definitions as being from indigenous or immigrant descent). In total, across sites and sub-sites, there are 72 strata. For each stratum, the database computer generated 50 independent randomisations. For each site except one in France, we have two randomisation arms (MDFT vs. TAU) and we use block randomisation with randomly permuted blocks of 2 or 4 cases. For one site in France, where there are three randomisation arms (MDFT, TAU and TAU-e; see below), we use blocks of 3 or 6 cases.

Randomization is concealed. A researcher enters new cases into the database, through her site's internet location, as soon as informed consent has been obtained, providing data on the stratification variables. Case code and randomization outcome are given automatically and right away, enabling the researcher to inform the family and to schedule appointments with the proper therapist without delay.

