### Blinding

Given the nature of the interventions, local researchers cannot be blinded as to the treatment delivered. Central research staff will be unaware of treatment condition when carrying out analyses to assess outcomes.

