### Assessments

Assessments take place at baseline and at 3, 6, 9 and 12 months post-randomization, at the treatment centre, the home of the family or any other convenient place. Additional information is gathered by phone or mail. Questionnaires are self-administered by the adolescent or parent, or if required completed by a researcher, who has been trained by INCANT project staff and is working under the guidance of three Instruction Manuals (for baseline, 3-months FU, and later FU, respectively; http://incant.eu). Table 1 shows the questionnaires and interviews delivered.

**Table 1 T1:** Measures used in INCANT at baseline and at four post-randomization follow-up points

Surveys	Baseline	Month 3	Month 6	Month 9	Month 12

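### Local researchers are said to be unblindable because of the interventions, but part of the unmasking comes from an avoidable routing of the allocation to the site researcher

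*Protocol article*

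**What the plan says.** All references are to the protocol article, Methods/Design.

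- **Randomization.** The site researcher requests the allocation: "A researcher enters new cases into the database, through her site's internet location, as soon as informed consent has been obtained". The same person receives it at once from the database, "enabling the researcher to inform the family and to schedule appointments with the proper therapist without delay".
- **Central database.** "Each site has one or two researchers authorized to access their own site's internet based location".
- **Assessments.** Questionnaires are filled in by the adolescent or parent, "or if required completed by a researcher, who has been trained by INCANT project staff". No separate or masked assessor is described.
- **Blinding.** "Given the nature of the interventions, local researchers cannot be blinded as to the treatment delivered". The only masking planned is at analysis: "Central research staff will be unaware of treatment condition when carrying out analyses to assess outcomes".
- **Recruitment.** The first session, where eligibility is checked, "is carried out by the clinical supervisor of the treatment centre, except in Brussels", where the INCANT researcher does it.
- **Primary outcomes: cannabis use.** Diagnosis comes from the ADI-Light, a structured interview. Frequency of use comes from the TLFB, a 90-day recall supported by a calendar and other prompts.

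**The concern.** The contrast between family therapy and individual counselling explains why therapists and families know the arm. It does not explain why the person who may later collect the outcome has to be told it at randomisation. The Blinding section therefore presents as a necessity something that is in part a choice of procedure.

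This matters because the TLFB and ADI-Light both leave room for an interviewer who knows the arm to prompt, probe or score differently. A difference introduced at data collection enters the MDFT–TAU contrast directly, and masking the central analysts cannot take it out again. The Sample size section says that the pooled analysis is powered assuming small effects, so even a modest recording difference could be a sizeable share of the effect sought.

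**Working it through.** **1. When does the researcher learn the arm?** Following Randomization in order: consent; the researcher enters the case; the database returns the case code and the arm; the researcher tells the family and books the therapist; treatment starts. The researcher is unmasked at the third step, before treatment has begun. At that moment the nature of the interventions has played no part.

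**2. Is this the person who assesses outcome?** Probably, but it is not stated. Three things point that way: only one or two researchers per site have database access, the same role is named in Randomization, Blinding and Assessments, and Blinding treats local researchers as unblinded without distinction. Against it, the count is of database users, not of assessment staff, and a site with two researchers could divide the tasks. No division is described.

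**3. What would remain if the routing were changed?** By visit, from Table 1 and the Measures section:

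| Visit | Primary instrument | Scheduled material likely to reveal the arm |
|---|---|---|
| Month 3 | TLFB | None (only TLFB and urine analyses are listed) |
| Month 6 | TLFB, PEI | Satisfaction Scales; Adolescent and Parent Interviews (service use) |
| Month 9 | TLFB, PEI | None new, but month 6 has passed |
| Month 12 | TLFB, PEI, ADI-Light | Adolescent and Parent Interviews (service use) |

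Rerouting can protect month 3, and month 6 as well if the TLFB is taken first. That covers baseline to month 6, the window of the main cannabis-use hypothesis in Study hypotheses. Taking the ADI-Light first at month 12 keeps that visit's interviews from revealing the arm, but cannot undo what an assessor saw at month 6.

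**4. Illustration of sensitivity.** The article gives no figure to reproduce here. Assumptions, none of them from the article: SD of 90-day use days 25 to 35; 450 cases (the article's minimum) split 1:1; simple two-arm comparison; two-sided 5%; small effect taken as d = 0.2.

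Shift δ = day difference / SD. Noncentrality λ = δ × √450 / 2. False-positive rate = Φ(λ − 1.96) + Φ(−λ − 1.96).

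| Difference | SD | δ | Share of d = 0.2 | λ | False-positive rate |
|---|---|---|---|---|---|
| 2 days | 25 | 0.080 | 40% | 0.849 | 0.136 |
| 2 days | 30 | 0.067 | 33% | 0.707 | 0.109 |
| 2 days | 35 | 0.057 | 29% | 0.606 | 0.093 |
| 3 days | 25 | 0.120 | 60% | 1.273 | 0.247 |
| 3 days | 30 | 0.100 | 50% | 1.061 | 0.185 |
| 3 days | 35 | 0.086 | 43% | 0.909 | 0.149 |

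For the month-12 diagnosis with 225 per arm and a 5-point scoring difference, λ = 0.05 / √(2p(1 − p)/225). At p = 0.3 or 0.7, λ = 1.157 and the rate is 0.212. At p = 0.5, λ = 1.061 and the rate is 0.186.

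These figures show what a bias of the assumed size would do. They do not show that one exists. The planned analyses are mixed and growth models, and one French site has three arms, so the simple comparison is only a rough guide.

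**The case against.** **The interventions do reveal the arm.** MDFT brings in parents and family, sometimes at home; TAU sessions are individual; both run in the same centres; and some forms ask about services and satisfaction. This stands. A reader might infer that routing is the true cause of the unmasking and that the stated reason is wrong. The document does not support that: the stated reason is incomplete, not false, and rerouting alone would not guarantee masked assessors.

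**The link to the interviewer is inferred.** This also stands. A reader might take it as established that every follow-up interviewer is unmasked by this step. The article never says who performs which follow-up, and many forms are self-completed.

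**The obvious alternative recipient is a poor one.** The clinical supervisor already meets each family outside Brussels. But that person checks eligibility, and allocation uses permuted blocks of 2 or 4 within strata (3 or 6 at the three-arm French site). Giving the screener the running allocations would make the next assignment easier to predict. This stands and shapes the fix.

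**The limitation is disclosed, and urine is tested at every assessment.** Both are true. However, open-label treatment does not require unmasked assessors. Urine results offer a check on self-report, but the primary-outcomes section does not name them as a measure of the primary outcome.

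**Conclusion.** The point holds in a limited form. The site researcher learns each allocation before treatment starts because the procedure delivers it to her, and the Blinding section leaves this out when it gives its reason. It is likely, though not stated, that the same one or two people collect the TLFB and ADI-Light. Part of the unmasking is therefore avoidable, chiefly at months 3 and 6.

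The size of any resulting bias is unknown. The 9–14% false-positive rate for a 2-day difference, 15–25% for 3 days and about 19–21% for a 5-point difference in diagnosis are consequences of assumed biases in a simple comparison, not estimates for this trial. Allocation concealment before enrolment is a separate matter and is not in question here. This is a worthwhile, inexpensive improvement and not a defect that invalidates the design.

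**What to change.** **Randomization section.** Have the database return only the case code to the researcher and send the allocation to an existing treatment-side staff member who neither screens families nor does follow-up assessments. The treatment team's coordinator is one example; the supervisor who runs the first session should not be used. That person informs the family and books the therapist. At sites with two researchers, an alternative is for the one who did not enter the case to do the follow-up TLFB and ADI-Light, with the allocation hidden from that login.

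**Blinding section.** Replace the statement that local researchers are unblindable with the following:

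- assessors are masked where possible;
- families are asked not to reveal their arm;
- the TLFB, and at month 12 also the ADI-Light, is completed first at each visit;
- the month-6 satisfaction and service-use forms are self-completed and returned sealed or by mail where possible;
- each unmasking is recorded.

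**Cost.** A change to where the database sends the allocation, a short amendment to the two sections and a little treatment-staff time. No extra visits or participants. Masking will be incomplete, especially after month 6. As enrolment is already under way, only cases still to be randomised or assessed would benefit.
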